#### Intervention period

The intervention period will start immediately after the baseline assessment for participants assigned to the intervention group. These will be introduced into the ABCC tool and will provide guidance on how to use it. The control group continued to receive usual care.

#### Follow-up assessments and visits

All participants (both intervention and control groups) will undergo follow-up assessments at 6, 12, and 18 months post-baseline. These assessments measure the following.Perceived quality of care using the PACIC.Health-related quality of life using the EQ-5D-5L.Patient activation using the PAM.

At each follow-up visit, any changes or updates to participants’ health conditions or care regimens were noted. Follow-up visits will also serve as opportunities for researchers to address any questions or concerns that the participants may have and ensure that the participants in the intervention group used the ABCC tool correctly.

#### End of study

The study will conclude after the 18-month follow-up assessment, at which point the primary and secondary outcomes will be evaluated. The primary outcome will be the perceived quality of care as measured by PACIC for the entire participant group and for each chronic condition separately. Changes in quality of life (EQ-5D-5L) and patient activation (PAM) at different time points led to secondary outcomes.

The expected duration of the entire study, including the enrollment, intervention, evaluation, and close-out phases, is expected to be two and a half years. This timeframe includes the pre-allocation preparation phase, the 18-month period for implementation of interventions and conduct of assessments, and additional months for initial recruitment and final analysis.

### Sample size {14}

The sample size estimation was guided by analogous assumptions from a concurrent study conducted in the Netherlands, thereby offering a relevant frame of reference for our calculations. The study’s primary outcome will be determined through the Patient Assessment of Chronic Illness Care (PACIC) measure. Given the lack of substantial data on the minimum significant difference and standard deviation for the PACIC in this specific population, an estimated medium effect size of 0.51 is derived from the work of Slok et al. [26]. This is based on an observed mean difference of 0.49 between the intervention and control groups, and a pooled within-group standard deviation of 0.96 from the same study.

For the current study, using an independent samples *t*-test, a significance level of 0.05 for two-sided testing, a power of 90%, and an even split between intervention and control groups, it is estimated that each group should include 82 patients. However, as patients will be grouped within general practices, this number is adjusted to account for the design effect, which is calculated as 1 + (m − 1) × ICC (intraclass correlation), where an ICC of 0.05 and an average of 10 patients per general practice is assumed [6].

After adjusting for cluster design (multiplication factor of 1.45), variable cluster sizes (division by 0.9), and an anticipated dropout rate of 25% (division by 0.75), it was estimated that each group would require 177 participants. Each group will need to include 18 general practices with an average of 10 patients per general practice. Therefore, 360 participants (180 per group) from 36 general practices (18 per group) will be recruited for this cluster-randomized study.

The aim was to achieve a balanced distribution among the various chronic conditions. However, given that healthcare providers are not explicitly instructed to strive to achieve this balance, this may not be ensured.

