### Eligibility criteria {10}

Eligibility criteria include patients with a diagnosis of chronic obstructive pulmonary disease (COPD), asthma, type 2 diabetes mellitus (T2DM), and/or heart failure, who are 18 years of age or older, and who understand and read German or Italian. Exclusion criteria include patients with asthma or COPD who had taken prednisone for an exacerbation within 6 weeks prior to the start of the study and patients with T2DM or heart failure who had been hospitalized within 6 weeks prior to the start of the study.

Eligibility criteria for participants will be validated through manual chart review, owing to the variability in software programs used across general practices and the lack of a unified EHR system in the region.

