## Statistical methods

### Statistical methods for primary and secondary outcomes {20a}

The data evaluation process is based on the intention-to-treat principle. Initial analyses will be performed on the entire group of patients with COPD, asthma, type 2 diabetes, and heart failure, which also includes those with multiple conditions. Subsequently, the impact of the ABCC tool is examined separately for patients with COPD, asthma, type 2 diabetes, and heart failure, irrespective of the presence of coexisting conditions.

Considering the clustered design of the study, a three-level multilevel analysis will be conducted: general practice, patient, and measurement. The study will apply linear mixed models to analyze outcomes to account for the grouping of measurements within patients in general practice. Fixed factors will include “treatment group,” “time” (categorical), and “interaction between treatment group and time.”

Given that randomization of patients into the intervention or control groups is not feasible, factors believed or known to influence the perceived quality of care and/or the use of the ABCC tool will be regarded as potential confounders. The intervention or control group assignment hinges on the accessibility of the ABCC tool (i.e., the presence of the ABCC tool tablet PC in general practice). Potential confounders include ethnic background (native/Western foreigner/non-Western foreigners), multimorbidity (yes/no), educational status (low/middle/high), age (continuous in years), sex (male/female), body mass index (BMI, kg/m2, continuous), smoking habits (never/former/current), location of the general practice (urban/rural), year of the general practitioner’s graduation (less/more than 10 years ago), and general practice in a group setting (yes/no).

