First, the implementation of the ABCC tool in general practice is a key operational aspect of this study. Given that the tool is new to the South Tyrolean Health Service, its integration within the clinical workflow of different practices might pose a challenge [33]. It will be crucial to ensure appropriate training for general practitioners and their teams to effectively use the tool and interpret results. Our implementation strategy for the ABCC tool within general practices aims to seamlessly integrate its use during face-to-face consultations. General practitioners will review the results of the ABCC tool with participants immediately, utilizing it as a dynamic component of the patient-provider interaction. This immediate feedback mechanism is designed to enhance shared decision-making and encourage patient self-management in real-time. Furthermore, while the tool is intended to be a valuable resource throughout the patient–provider relationship, its use in each visit will be at the discretion of the healthcare provider, based on the relevance to the patient’s current care needs and consultation focus. This flexible approach aligns with our goal to validate the effectiveness and cost-effectiveness of the ABCC tool in enhancing perceived quality of care and quality of life, as observed in Dutch studies, within the distinct context of the South Tyrolean healthcare system. Successful integration and positive outcomes from this study will inform broader implementation strategies, aiming for a patient-centered and economically beneficial tool across healthcare settings.

Second, the recruitment of a diverse range of general practices, both urban and rural, across different language groups is fundamental to the generalizability of the results [34]. Achieving this diversity might be challenging, given the voluntary nature of participation. Moreover, within each practice, it is important to ensure a balanced representation of patients with different chronic conditions that requires careful management and supervision. To ensure a balanced representation of patients with different chronic conditions within each practice, we will engage with general practitioners to promote the enrollment of a diverse patient cohort. This strategy complements the stratified randomization process, aiming to achieve a comprehensive assessment of the ABCC tool’s impact across the spectrum of chronic conditions addressed in our study.

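### The protocol is inconsistent on whether GPs are steered towards a balanced mix of conditions, and the pooled model has no term for condition

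*Protocol article*

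**What the plan says.** Sample size {14} states a goal, "The aim was to achieve a balanced distribution among the various chronic conditions", and then qualifies it: "given that healthcare providers are not explicitly instructed to strive to achieve this balance, this may not be ensured".

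The Discussion, in its second operational point, says that within each practice "it is important to ensure a balanced representation of patients with different chronic conditions that requires careful management and supervision". It continues: "To ensure a balanced representation of patients with different chronic conditions within each practice, we will engage with general practitioners", the means being "to promote the enrollment of a diverse patient cohort". It adds that this complements the stratified randomization. Neither section gives a quota, target share or selection procedure.

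Other sections bear on the point:

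- **Population.** Eligibility criteria {10}: "Eligibility criteria include patients with a diagnosis of chronic obstructive pulmonary disease (COPD), asthma, type 2 diabetes mellitus (T2DM), and/or heart failure".
- **Analysis sets.** Statistical methods {20a}: "Initial analyses will be performed on the entire group of patients with COPD, asthma, type 2 diabetes, and heart failure", multimorbid patients included. Each condition is then analysed separately, regardless of comorbidity.
- **Order of events.** Study setting {9} and the enrollment paragraph under Participant timeline {13} place patient recruitment after practice randomization. Who will be blinded {17a} says that patients and providers are not blinded.
- **Model.** The fixed factors in {20a} are group, time and their interaction. Sequence generation {16a} adds the stratification variables: language, location, and GP sex and age. The named candidate confounders in {20a} and {20b} include multimorbidity yes/no but not diagnosis.
- **Data.** Table 2 records chronic condition at time 0.

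**The concern.** Someone writing the recruitment instructions for practices cannot tell from these two sections whether GPs are to be steered towards balance. One section says they are not told to seek it and that it may not be reached. The other describes supervised effort to ensure it.

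The pooled PACIC effect is an average over whatever mix is enrolled. Practices know their arm when they approach patients, so a vague instruction can be acted on differently in the two arms. If patients with different conditions rate their care differently, a difference in mix between arms enters the group comparison. The named adjustment variables would not remove it, because multimorbidity yes/no does not distinguish, for example, asthma alone from heart failure alone.

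The mix also sets how many patients each per-condition analysis has, and so its precision.

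**Working it through.** **1. Does the sample size depend on the mix?** Inputs from Sample size {14}: d = 0.49/0.96 = 0.51, two-sided alpha 0.05, power 90%, ICC 0.05, 10 patients per practice, factor 0.9 for variable cluster sizes, 25% dropout.

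- The t-test solution is n = 81.8, so 82 per group. This matches the plan.
- Design effect: 1 + (10 − 1) × 0.05 = 1.45.
- 82 × 1.45 / 0.9 / 0.75 = 176.1, so 177. This matches the plan.
- 18 practices × 10 = 180 per group, 360 in total.

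No step uses the mix of conditions, so the target stands under either statement.

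**2. Are the analysis sets fixed?** Yes. {10} and {20a} define the pooled set and each per-condition set by diagnosis. The mix changes their size and weight, not their membership rule.

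**3. What could a difference in mix do to the pooled effect?** Let p_Ik and p_Ck be the proportions with condition k in the two arms, and β_k the PACIC difference associated with that condition. A model without condition shifts the group difference at a visit by about

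Σ_k (p_Ik − p_Ck) × β_k.

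The documents give neither the proportions nor β_k, so no number can be attached. If baseline is one of the levels of time and the effect is read as change from baseline, a β_k that is constant over time cancels. What remains is any difference between conditions in how PACIC changes.

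**4. Per-condition precision (illustration).** The document gives no shares, so the share s is assumed. Effective n per arm = 180 × s × 0.75 × 0.9 / DE, with DE = max(1, 1 + (10s − 1) × 0.05). Power is from the two-sample t-test at d = 0.51. The 95% half-width is 1.96 × 0.96 × √(2/n).

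| Share s | Analysed per arm | DE | Effective n | Power | Half-width (PACIC points) |
|---|---|---|---|---|---|
| 0.10 | 13.5 | 1 | 12.2 | 0.225 | 0.76 |
| 0.15 | 20.25 | 1.025 | 17.8 | 0.315 | 0.63 |
| 0.25 | 33.75 | 1.075 | 28.3 | 0.469 | 0.50 |
| 0.40 | 54.0 | 1.15 | 42.3 | 0.639 | 0.41 |
| 1.00 (all) | 135 | 1.45 | 83.8 | 0.907 | 0.29 |

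A 25% share is an equal split with no overlap. Under {20a} a patient counts in the set of every diagnosis held, so shares can sum to more than 100%. The lower rows therefore matter as much as the upper ones.

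**The case against.** The strongest reply is that the two sections share an aim and differ mainly in tone. Encouraging GPs without a binding instruction is compatible with both, and the Discussion offers only promotion as its means. That largely stands. What remains is one section setting out to ensure balance and the other conceding that it may not be ensured.

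A reader might infer stronger things that the documents do not support:

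- **That these are opposite rules giving different samples.** Neither section sets a share or quota, so neither fixes a mix.
- **That the population is undefined.** Diagnosis defines eligibility and every analysis set. An unconstrained mix is ordinary in a pragmatic trial, and {14} discloses it.
- **That condition is said to be a stratification factor.** The Discussion says only that engagement complements stratified randomization.
- **That the arms will differ in mix.** Nothing says engagement will vary by arm, and Implementation {16c} has the research team manage enrollment. The route is open because practices recruit and take consent knowing their allocation, but this is a risk, not a demonstrated bias.
- **That quotas would rescue the per-condition analyses.** Equal non-overlapping shares still give only about 47% power.

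It is also fair to say that {20a} describes candidate confounders broadly, as factors thought to affect perceived care, and that the weighting analysis could take in condition. But {20a} then lists the candidates, and diagnosis is not among them.

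**Conclusion.** The point holds as a minor inconsistency with an inexpensive improvement attached. {14} and the Discussion should say the same thing about steering the mix. Separately, the stated pooled model and its named confounders have no term for condition, although unblinded practices recruit after allocation and the variable is recorded at baseline.

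The sample size reproduces (82, then 177 per group) and is unaffected, as are the definitions of the analysis sets. The size of any bias in the pooled effect cannot be derived from the documents.

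The per-condition power of about 23% to 47% is illustrative. It rests on assumed non-overlapping shares of 10% to 25% and the plan's own d, SD, ICC, dropout and cluster-size factor. It rises with overlap, to 64% at a 40% share for example. It does not measure the harm from the inconsistent wording, since equal shares would not bring these analyses to 90%.

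**What to change.** 1. **Model.** In {20a}, prespecify baseline condition as fixed covariates in the pooled linear mixed model, outside the p ≤ 0.05 screen. Use four yes/no indicators, because conditions overlap and a single category would not represent multimorbid patients. If baseline is a level of time, add their interaction with time, because main effects alone would do little to a change-from-baseline contrast.
2. **Wording.** Replace the statements in {14} and the Discussion with one recruitment statement applied identically in both arms. Either accept the natural practice mix and drop the claim to ensure balance, or give all practices the same encouragement and say that balance is not guaranteed.

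The cost is a few sentences and a few model parameters. Table 2 already collects the variable, and Trial status says recruitment had not begun.

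A quota per condition with random-order invitation is not required. It would give up the natural case mix of a pragmatic trial. It would also require listing eligible patients by condition in 36 practices, whereas {10} plans manual chart review only to validate eligibility.

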### Recruitment {15}

Several strategies will be employed to ensure that the target sample size is reached. The existing relationships between health networks and medical associations in South Tyrol will also be leveraged. The research team will directly contact general practitioners in South Tyrol to invite them to participate in the study through meetings, letters, email, and phone calls. The aim is to provide them with detailed information about the study, address any concerns, and encourage them to enroll their patients. While maintaining ethical considerations, we may provide appropriate incentives to general practitioners for their involvement in the study, including recognizing their contribution to the study, offering educational opportunities related to chronic disease management, and reporting findings that might be beneficial for their practice. Once general practitioners agree to participate, they are effectively “consented” into the study and the research team will maintain regular communication with them to ensure that they have the necessary support to recruit and enroll patients, and address any issues that may arise during the study period.

Patient understanding and consent are crucial for patient enrollment. Thus, we will ensure that potential patients receive clear, easy-to-understand information about the study, its benefits, and what their involvement entails. Patient participants will be given sufficient time to consider their participation and ask questions.

These strategies are dynamically adapted based on the enrollment rate to ensure that the target sample size is achieved within the planned timeline.

## Assignment of interventions: allocation

### Sequence generation {16a}

In this cluster-randomized trial, general practices throughout South Tyrol serve as the unit of randomization. After recruitment, these practices will be assigned to either the intervention or control group through a stratified randomization process. Stratification factors include the patients’ preferred language (Italian or German), the location of the practice (urban or rural), and the demographic characteristics of the general practitioners (sex and age). Sequences will be generated using computer software to pre-generate random assignments. Practices in the intervention group will use the ABCC tool via a provided tablet PC, while those in the control group will continue their usual care without access to the tool.

To maintain the integrity of this randomization process and control for potential confounding, these stratifying variables will be explicitly included in the analytical models.

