Each potential confounder will be independently added to the aforementioned linear mixed model, and if it is significantly associated with the outcome (*p* ≤ 0.05), it will be considered a confounder. Both unadjusted and adjusted treatment effects will be reported along with their corresponding 95% confidence intervals and *p*-values. Statistical significance is set at *p* < 0.05. To account for multiple potential confounders, inverse probability of treatment weighting using propensity scores will be used as a sensitivity analysis. The use of hierarchical modeling aims to methodically evaluate the significance of confounders, prioritizing them by their theoretical relevance and observed impact on study outcomes. To ensure analytical robustness, R-squared values will further quantify each covariate’s contribution to the model.

The primary outcome will encompass all measurement times, including data collected at 6, 12, and 18 months. The analytic strategy will use longitudinal data collected at 6, 12, and 18 months, incorporating random effects models to account for the nesting of patients within practices. Model comparison techniques will be used to assess the fit of increasingly complex models to ensure that the analysis captures the impact of the intervention while accounting for provider variability within practices.

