### Methods for additional analyses (e.g., subgroup analyses) {20b}

In addition to the secondary objective of assessing the shift in perceived quality of care, employing the PACIC against regular care after 18 months, individually for each chronic condition, further subgroup analyses will be conducted based on age, sex, multimorbidity status, and educational level, as these factors could potentially influence perceived quality of care and the use of the ABCC tool.

Linear mixed models are used for these analyses, with the subgroups added as interaction terms to assess whether the effect of the intervention varied across different subgroups. The subgroup analyses are specified a priori in the study protocol to avoid data dredging.

Adjusted analyses will also be conducted to control for potential confounders. Factors known or hypothesized to be associated with perceived quality of care or the use of the ABCC tool will be considered potential confounders and adjusted for in the analysis, including national background, location of general practice, year of graduation of the general practitioner, and whether the general practice is part of a group.

For adjusted analyses, especially when significant confounders are identified, the Inverse Probability of Treatment Weighting method will be used as described by Hernán et al. [29]. This approach, designed to balance the distribution of observed baseline covariates across treatment groups, mitigates potential bias and is fundamental to estimating the causal effects of interventions.

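### The randomisation section promises that all stratification factors enter the models, but the model section keeps practice location only if p ≤ 0.05 and does not carry through language, GP sex or GP age

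*Protocol article*

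**What the plan says.** Sequence generation {16a} lists four factors: "Stratification factors include the patients’ preferred language (Italian or German"), then "the location of the practice (urban or rural), and the demographic characteristics of the general practitioners (sex and age"). It adds, without any condition, that "these stratifying variables will be explicitly included in the analytical models". Concealment mechanism {16b} confirms that these characteristics are collected and entered into the randomisation software.

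Statistical methods {20a} describes the linear mixed model: "Fixed factors will include “treatment group,” “time” (categorical), and “interaction between treatment group and time". It then lists potential confounders. The practice-level items are "location of the general practice (urban/rural), year of the general practitioner’s graduation (less/more than 10 years ago), and general practice in a group setting". Age and sex also appear in that list, but next to BMI and smoking, so they are patient characteristics. The rule for keeping an item is: "Each potential confounder will be independently added to the aforementioned linear mixed model, and if it is significantly associated with the outcome" at p ≤ 0.05. Unadjusted and adjusted effects are both to be reported, and neither is named as primary.

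Methods for additional analyses {20b} gives a further adjustment list, "including national background, location of general practice, year of graduation of the general practitioner, and whether the general practice is part of a group". It too lacks language, GP sex and GP age.

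**The concern.** For location, the two sections give rules that cannot both be followed: always in the model, or in the model only if significant. For language, GP sex and GP age, {16a} makes a promise that the later sections do not pick up. Graduation year, split at 10 years, is only a partial stand-in for GP age. An analyst working from {20a} would therefore fit a model that departs from {16a}, and the protocol does not settle which covariates belong to the primary effect.

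What is at stake is precision. Stratified randomisation balances the factors between arms, which lowers the true variance of the treatment effect if the factors predict the outcome. A model without them leaves their variance in the between-practice error. The standard error is then larger than it should be, the test runs below its nominal level, and some power is lost. Letting an outcome p-value decide on a design factor also makes the primary model depend on the data.

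**Working it through.** **Text, factor by factor**

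| Stratification factor in {16a} | {20a} | {20b} adjustment list |
|---|---|---|
| Language | not named | not named |
| Location | kept only if p ≤ 0.05 | named |
| GP sex | not named | not named |
| GP age | not named (graduation year only) | not named (graduation year only) |

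**The plan's own sample size.** Inputs from Sample size {14}: difference 0.49, SD 0.96 (d = 0.51), two-sided 0.05, power 90%, ICC 0.05, 10 patients per practice, division by 0.9 and by 0.75. An exact t-test calculation gives 82 per group. The design effect is 1 + 9 × 0.05 = 1.45, and 82 × 1.45 / 0.9 / 0.75 = 176.1, so 177, or 18 practices per group. The stated figures reproduce. They use no covariates, so this point does not change the sample size.

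**Standard error by formula.** Take 18 practices per group and 10 × 0.75 = 7.5 evaluable patients per practice.

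- Between-practice variance: 0.05 × 0.96² = 0.0461.
- Within-practice variance of a practice mean: 0.95 × 0.96² / 7.5 = 0.1167.
- Total: 0.1628. SE of the difference: √(2 × 0.1628 / 18) = 0.1345.

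If the strata explain a share R² of the between-practice variance and are perfectly balanced, the true variance of a practice mean is 0.1628 − R² × 0.0461. A model without strata still reports about 0.1345. The ratio of reported to true SE is then:

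- R² = 0.25: √(0.1628 / 0.1513) = 1.04
- R² = 0.50: √(0.1628 / 0.1398) = 1.08
- R² = 0.90: √(0.1628 / 0.1213) = 1.16

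These overstate the effect. Four binary factors make 16 cells for 36 practices, so balance is incomplete.

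**Simulation with realistic balance.** 8,000 trials per setting, analysed on practice means at a single follow-up with no treatment effect. Assumptions: four binary factors, permuted blocks of two within the 16 cells, and R² as shown. Ratios are model SE over empirical SE. The Monte Carlo standard error of the type I error is about 0.2 percentage points.

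| R² | No strata terms: SEs, ratio, type I | Location only if p ≤ 0.05: ratio, type I | All four terms: ratio, type I |
|---|---|---|---|
| 0 | 0.1346 / 0.1344 = 1.00, 5.0% | 1.00, 5.1% | 1.00, 4.7% |
| 0.25 | 0.1348 / 0.1309 = 1.03, 4.4% | 1.02, 4.6% | 1.00, 5.0% |
| 0.50 | 0.1351 / 0.1271 = 1.06, 3.7% | 1.04, 4.0% | 1.01, 4.8% |
| 0.90 | 0.1353 / 0.1215 = 1.11, 3.0% | 1.08, 3.5% | 1.00, 5.0% |

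At an assumed ICC of 0.10, the ratios without strata terms are 1.00, 1.05, 1.11 and 1.22.

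**Change from baseline.** If baseline is a level of time and the effect is read from the group-by-time term, a language or location gap that is constant over time drops out. In SD units, with an assumed within-patient correlation of 0.5 and a constant practice effect, the variance of a practice-mean change is 2 × 0.95 × (1 − 0.5) / 7.5 = 0.127, and the SE is √(2 × 0.127 / 18) = 0.119. A simulation with a language gap of 0.3 or 0.5 SD gave 0.118 with and without strata terms, and a type I error of 5% both ways.

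**The case against.** The strongest reply is that most of this is silence, not contradiction. The fixed factors in {20a} are introduced with wording that does not exclude others, and the list that follows concerns potential confounders, a different role from stratifiers. An analyst could add language, GP sex and GP age as {16a} requires and breach nothing. The separate analysis plan may also spell this out. That stands for those three factors: they are not carried through, but they are not excluded either. It does not stand for location, where one section says always and the other says only if significant.

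A reader might infer that the trial's confidence intervals will be too wide. The documents do not support that as a fact. It needs {20a} to be followed over {16a}, and it needs strata that predict PACIC, on which the protocol gives no figure. It also depends on the contrast. The abstract and Outcomes {12} speak of change over 18 months, and PACIC is measured at baseline, while {20a} describes the longitudinal data as those at 6, 12 and 18 months. If baseline enters as a level of time, the loss largely disappears.

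A reader might also infer that planned power is at risk, because a language gap would raise the ICC. A 0.3 SD gap added to an ICC of 0.05 gives (0.05 + 0.0225) / 1.0225 = 0.071 and a design effect of 1.64. This treats 0.05 as the ICC after language is removed, which Sample size {14} does not say. Even on that assumption, with gaps of 0.3 SD for language and 0.2 SD for location, simulated power at d = 0.51 is 92% without strata terms and 94.5% with them, both above 90%.

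**Conclusion.** The inconsistency is definite for location and an omission for language, GP sex and GP age. Following {20a} brings no bias and no excess false positives from this source. Any error is conservative: at ICC 0.05 the standard error is 0% to 11% too large without strata terms, and 0% to 8% too large with location screened, as the strata explain 0% to 90% of between-practice variance. These figures rest on assumed shares, 7.5 evaluable patients per practice, binary factors and a follow-up-only contrast. For change from baseline, or for strata unrelated to PACIC, the loss is little or none. This should be corrected because the protocol contradicts itself on what is in the primary model and the correction is nearly free.

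**What to change.** - In {20a}, pre-specify the factors actually used in the randomisation (language, location, GP sex, GP age) as fixed covariates in the primary and secondary models, regardless of p-value. Enter them as main effects, since 16 or more cells are too many for 36 practices.
- Remove location from the list screened at p ≤ 0.05.
- Align the adjustment list in {20b}.
- Name the strata-adjusted effect as the primary result, with the unadjusted effect as supporting.

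The cost is wording and about 4 of the 36 − 2 = 34 between-practice degrees of freedom. With no prognostic strata, the simulated model SE rises only from 0.1346 to 0.1366. The variables are already collected for the randomisation, and Trial status reports that recruitment had not begun.
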